**Primary outcome**												
	ICP	Lumbar puncture	X								X	
**Secondary outcomes**												
	Anthropometric measures	Body mass index, blood pressure, waist/hip, body composition	X								X	X
	IIH symptoms	Pulsatile tinnitus, visual loss, diplopia, visual obscurations	X								X	X
	Visual function	Visual acuity, contrast sensitivity	X								X	X
		Humphrey visual field (24-2)	X								X	X
	Papilledema	Optical coherence tomography	X								X	X
		Retinal photographs	X								X	X
	Headache	HIT-6, headache index, analgesia use	X								X	X
	Medical assessment	History, +/- examination, compliance	X	X	X	X	X	X	X	X	X	X
		Safety bloods	X	X			X		X		X	X
		Pregnancy test	X	X			X		X		X	X
**Exploratory outcomes**												
	Global 11β-HSD1 activity	24-hour urine	X	X			X		X		X	X
	Hepatic 11β-HSD1 activity	Prednisone to prednisolone measurements in serum	X								X	
	Adipose 11β-HSD1 activity	Subcutaneous adipose biopsy	X								X	
	Body habitus	DXA	X								X	
	Pharmacokinetic analysis	Plasma and CSF	X	X							X	

**Figure 2 figure2:**
[figure not shown]
Overview of the screening visit.

#### Subsequent Visits

The treatment period is 12 weeks. Participants will be assessed at 1, 2, 3, 4, 6, 8, 10, 12, and 16 weeks (see Table 2). All visits will determine adverse events and treatment compliance. Visits 1, 4, 8, 12, and 16 will require safety and hormone bloods as well as a urinary pregnancy test. The 12-week visit will repeat the screening visit. Following 4 weeks off the trial drug, patients will be assessed at 16 weeks for visual tests, headaches, bloods, IIH symptoms, and adverse events. The follow-up visit at Week 16 is deemed sufficient time for the effects of the trial drug to have dissipated. Any relapses in IIH-related symptoms are then determined.

### Statistical Methods

The primary analysis of efficacy is based on the full analysis set, as defined by ICH guidance document *E9: Statistical Principles for Clinical Trials*. This analysis adheres as closely as possible to the intention-to-treat ideal and is based on data from all randomized participants with participants analyzed in the treatment group to which they were randomized.

### Primary and Secondary Outcome Analyses

The primary comparison groups are composed of those randomized to AZD4017 versus placebo. For all major outcome measures, summary statistics and differences between groups (eg, mean differences) will be presented with 95% confidence intervals and *P* values from two-sided tests. No adjustment for multiple comparisons will be made.

The primary outcome examines the effect of AZD4017 on ICP from baseline to 12 weeks postrandomization. Data will be reported with means and standard deviations or medians and ranges for nonparametric data. The ICP at 12 weeks for the two trial arms will be compared using a linear regression model with baseline ICP included as a covariate in the model.

Secondary outcome measures are analyzed at 12 and 16 weeks. The majority of secondary outcomes are continuous data items, which will be analyzed as per the primary outcome. For the visual function data that are collected in both eyes, it is expected that the participant’s data will be correlated, so the primary analyses will use data from both eyes and will be analyzed using a linear mixed model, with participants included as a random effect. The visual function data for each eye will also be analyzed separately as per the primary outcome, but this will be a secondary analysis. The IIH symptom data is binary and will be analyzed using log-binomial models with baseline symptom included in the model as a covariate.

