### Eligibility

Patients are recruited based on the presence of active IIH, either newly diagnosed or a long-standing diagnosis, with any degree of visual loss and fulfillment of the trial inclusion and exclusion criteria (Table 1; [16]). As IIH predominantly affects obese females of child-bearing age, this will be the focus of the trial. Males and children tend to present differently with atypical features and may have an alternative pathogenesis [17] and so are excluded.

During the trial, the HPA hormones are monitored. We have excluded those on glucocorticoid and other hormonal medications as this may confound monitoring of the HPA axis. Those on mild topical steroid preparations or on inhaled steroids for asthma have been included as the systemic levels are low. The inclusion of IIH patients on acetazolamide and other diuretics is permitted if the participant is on a stable dose.

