#### Secondary Outcomes

Raised ICP underlies the symptoms and signs of IIH, thus alterations in ICP should result in clinical fluctuations. The following secondary outcomes are recorded:

IIH symptoms (presence or absence of tinnitus, visual loss, diplopia, visual obscurations, and headache)IIH visual function in both eyes (measured by log of the minimum angle of resolution charts to assess visual acuity, automated perimetry [Humphrey 24-2 central threshold] to measure the visual field mean deviation and MARs charts to evaluate contrast sensitivity)papilledema is evaluated using spectral domain optical coherence tomography (Spectralis, Heidelberg Engineering) and fundal photographs with Frisen classification (by masked neuro-ophthalmologists) to grade the imagesheadache-associated disability through the headache impact test-6 score (HIT 6), headache severity, frequency, and the use of analgesia (days/weeks)anthropological measures (blood pressure, body mass index, waist/hip ratio)safety and tolerability profile of AZD4017 through adverse event reporting and safety bloods (see Table 2)

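### The lead both-eyes model for visual function names no baseline term, although the ICP, symptom and single-eye analyses are baseline-adjusted; run as written it loses precision

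*Protocol article*

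**What the plan says.** All the models are in the protocol article under Primary and Secondary Outcome Analyses.

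- **ICP (primary outcome):** the arms are "compared using a linear regression model with baseline ICP included as a covariate in the model".
- **Continuous secondary outcomes in general:** "The majority of secondary outcomes are continuous data items, which will be analyzed as per the primary outcome".
- **Visual function, lead analysis:** because the two eyes of a participant are correlated, the primary analyses "will use data from both eyes and will be analyzed using a linear mixed model, with participants included as a random effect".
- **Visual function, each eye alone:** "The visual function data for each eye will also be analyzed separately as per the primary outcome, but this will be a secondary analysis".
- **Symptoms:** "log-binomial models with baseline symptom included in the model as a covariate".

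The Eligibility section admits patients "either newly diagnosed or a long-standing diagnosis, with any degree of visual loss". Screening data serve as baseline, and Table 2 schedules acuity, contrast sensitivity and visual field at Weeks 0, 12 and 16.

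**The concern.** Of the models set out in that section, only the both-eyes visual model has no baseline value, whether named or brought in by reference. Its participant random effect deals with the correlation between a person's two eyes. It does not remove the differences in vision that people bring into the trial.

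Those differences are likely to be wide, given the entry criteria, and about 24 evaluable participants are planned. If the model were fitted as worded, variation already present at entry would stay in the error term of the lead analysis of acuity, visual field and contrast sensitivity. These outcomes bear on whether a change in ICP carries through to vision. The wording also leaves a choice between adjusted and unadjusted results that could be made after the data are seen.

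**Working it through.** **1. The plan's own figure.** The only stated calculation is for ICP (Sample Size): difference 14%, SD 10%, 90% power, alpha 0.05. The normal approximation is n per arm = 2 × (1.960 + 1.282)² × (10/14)² = 10.7, so 11. The two-sample t test gives 87.7% power at 11 per arm and 90.6% at 12. With 20% dropout, 24/(1 − 0.20) = 30. The figure reproduces. It says nothing about visual function, for which no figure is given.

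**2. Inputs for the visual model.** From the article: 12 evaluable participants per arm, two eyes each, two-sided 5% tests. Assumed: r, the correlation between baseline and Week 12 of a participant's two-eye mean, varied from 0.3 to 0.9.

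**3. Formula.** With both eyes measured in everyone, the random-intercept test of treatment arm without baseline is equivalent to comparing participants' two-eye means. Adding baseline multiplies the variance of the treatment difference by (1 − r²). The ratio of standard errors, without to with baseline, is therefore 1/√(1 − r²). The between-eye correlation cancels.

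If the adjusted analysis had 90% power, the power of the unadjusted one would be Φ(3.242 × √(1 − r²) − 1.960).

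| Assumed r | SE ratio, without/with baseline | Unadjusted power if adjusted power is 90% |
|---|---|---|
| 0.3 | 1.05 | 87% |
| 0.5 | 1.15 | 80% |
| 0.7 | 1.40 | 64% |
| 0.8 | 1.67 | 49% |
| 0.9 | 2.29 | 29% |

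Worked line for r = 0.7: √(1 − 0.49) = 0.714; 1/0.714 = 1.40; 3.242 × 0.714 − 1.960 = 0.355; Φ(0.355) = 64%.

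**4. Check on validity.** Two-eye means were simulated with no treatment effect, 12 per arm, 20,000 runs for each r.

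| r | Type I error, unadjusted | Type I error, adjusted | SD of estimate, unadjusted | SD of estimate, adjusted |
|---|---|---|---|---|
| 0.5 | 5.0% | 5.3% | 0.409 | 0.362 |
| 0.8 | 4.9% | 5.0% | 0.406 | 0.251 |

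The mean estimated effect was within 0.003 of zero throughout. The simulated ratios are 0.409/0.362 = 1.13 and 0.406/0.251 = 1.62. They fall slightly below the formula's 1.15 and 1.67 because the baseline slope has to be estimated in a small sample.

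**5. Limit of the calculation.** It works on two-eye means. An eye-level baseline covariate gives about the same gain if the baseline slope is similar within and between participants.

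**The case against.** **The general rule may already supply the baseline term.** Most continuous secondary outcomes are to follow the primary model, which is baseline-adjusted. The mixed-model sentence can be read as adding only the handling of two eyes. Nor does it name treatment arm, so it is plainly not a full list of fixed effects. This stands so far as it goes: the text does not exclude baseline. It does not settle the matter, because the rule covers only a majority of outcomes, visual function is then given its own model, and the reference back to the primary outcome is repeated for the single-eye analyses. The repetition would be unnecessary if the rule already governed visual function.

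**This is a condensed article.** The full model may be in an analysis plan that is not shown. That is fair, and is why the point concerns uneven wording rather than missing detail: the article does give the covariate, directly or by reference, for the neighbouring models.

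**Adjusted visual estimates will exist anyway,** from each eye alone. True, but they are labelled secondary and each uses half the data.

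**A reader might infer more than the article supports:**

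- *That entry differences in vision would overwhelm any treatment effect, or bias the result.* The article gives no visual SD, effect size or correlation, and the unadjusted comparison is unbiased. Chance imbalance at entry is the same loss of precision, not a second fault.
- *That tomography would be analysed with both eyes pooled in ordinary regression, inflating type I error.* The Secondary Outcomes section says that "papilledema is evaluated using spectral domain optical coherence tomography". It does not state there whether one eye or both enter the analysis, and nothing in the article proposes such pooling.

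**Conclusion.** The point holds as one of inconsistent specification with a cost in precision. As worded, the lead visual function model has no stated baseline term while the ICP, symptom and single-eye analyses do. If it were run that way, type I error and unbiasedness would be preserved. The standard error would be larger by about 5% at an assumed correlation of 0.3, 15% at 0.5, 40% at 0.7 and 67% at 0.8.

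The size of the loss rests entirely on that assumed correlation: small if it is low, considerable if it is high. The participants' wide range of vision at entry makes a high value plausible but does not establish one. The matter is confined to secondary outcomes. Neither the primary ICP analysis nor the sample size is touched.

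**What to change.** State the model in full: the eye-level value at Week 12, and in a separate model at Week 16, regressed on treatment arm and that eye's own baseline value, with a participant random intercept. If a fuller analysis plan already says this, the article's wording only needs to be brought into line with it.

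The cost is one clause and one degree of freedom. No new data are needed, since Table 2 already schedules the visual tests at Week 0. Fixing the wording before unblinding also removes any later choice between adjusted and unadjusted results.

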### Study Withdrawal

Participants are free to withdraw from the study at any time. Such participants will always be asked about the reason(s) and the presence of any adverse events. If the participant is withdrawn from the trial by the investigator for any reason at any visit during the study, assessments for the early discontinuation visit will be completed during that visit, and the withdrawn participant asked to return for Visit 12 between 83 and 97 days, inclusive.

If the participant needs to be withdrawn from the active treatment phase between trial visits for safety reasons, trial medication will be stopped immediately and the participant will be instructed to attend the next arranged clinic visit, which will be treated as an early discontinuation visit. If it is considered appropriate by the investigator, more frequent or additional follow-up visits can be scheduled (if willing, the participant will be asked to attend the 12-week final trial visit). Withdrawn participants will not be replaced.

### Monitoring

#### Adverse Event Reporting

All serious adverse events (SAEs) must be reported, whether or not considered causally related to the trial drug or to study procedures. A clinician must assess the severity, causality, and expectedness of the SAE. If the event is considered to be related to the study drug, then the SAE will be classed as a serious adverse reaction (SAR). If the SAR is listed in the safety information of AZD4017, then it is listed as expected and included in the ongoing safety review of the study. If it is not an expected SAR for AZD4017, then it is listed as a suspected unexpected serious adverse reaction (SUSAR). The trial team will then be contacted to unblind the subject’s medication allocation. A fatal or life-threatening SUSAR will be reported to the Medicines and Healthcare Products Regulatory Agency and the research ethics committee within 7 days.

#### Unblinding

Investigators and subjects are unaware whether the product is AZD4017 or placebo (double-blinded); this information is held by local pharmacies in the form of scratchcards detailing the trial number and a scratch-off panel. Unblinding can take place in the case of a SUSAR and in medical emergencies, when knowing the treatment will change the management of the patient.

#### Monitoring Committees

A trial steering committee made up of independent members (including the chair) and trial team members provides oversight of the trial. An independent data monitoring committee (DMC) monitors unblinded efficacy and safety reports. If there are any major safety concerns, the DMC can recommend early discontinuation of the trial.

## Results

The trial opened March 2014 with the first patient recruited April 2014. Additional sites were opened at the Walton Centre, Liverpool (January 2016), Southern General Hospital, Glasgow (March 2016), and Royal Hallamshire Hospital, Sheffield (April 2016) to facilitate recruitment. The DMC and trial steering committee meet regularly to monitor the course of the IIH:DT. The trial results are expected in September 2017.

## Discussion

### Principal Considerations

Recruitment to IIH:DT was completed in August 2016. Results from the trial are still awaited. The two RCTs evaluating IIH treatments completed thus far have investigated an established drug, acetazolamide. IIH:DT is the first to assess the efficacy of a new drug treatment, an 11β-HSD1 inhibitor (AZD4017), not tested in IIH before. More importantly, it aims to establish the safety profile of AZD4017 in IIH. Safety monitoring involves regular safety bloods and adverse event recording. These are performed in accordance with prior AZD4017 study results. This is the longest period of time the drug has been administered to humans. Positive safety results will provide important information for future trials using AZD4017.

### Conclusions

IIH is in need of new treatments. IIH:DT is the first phase II double-blinded randomized placebo-controlled trial in IIH. It assesses a novel therapeutic pathway through inhibition of 11β-HSD1 by the drug AZD4017. In addition to the primary outcome of ICP, a range of secondary outcomes including visual function, headache, and papilledema will be assessed. IIH:DT aims to establish initial evidence of efficacy and safety that could lead to a future large phase III study using AZD4017 in IIH.

## Appendix

Multimedia Appendix 1 IIH:DT headache diary.

Multimedia Appendix 2 UK Medical Research Council (MRC) Reviewer comments.

## Abbreviations

BCTU: Birmingham Clinical Trials Unit
CSF: cerebrospinal fluid
CTA: clinical trial authorization
DMC: data monitoring committee
DXA: dual-energy x-ray absorptiometry
HIT-6: headache impact test 6
HPA: hypothalamic, pituitary, adrenal
11β-HSD1: 11beta-hydroxysteroid dehydrogenase type 1
ICP: intracranial pressure
IIH: idiopathic intracranial hypertension
IIH:DT: Idiopathic Intracranial Hypertension Drug Trial
IIHTT: Idiopathic Intracranial Hypertension Treatment Trial
LP: lumbar puncture
MRC: Medical Research Council
NHS: National Health Service
RCT: randomized controlled trial
SAE: serious adverse event
SAR: serious adverse reaction
SUSAR: suspected unexpected serious adverse reaction
